***(End Uganda site-specific information.)***

If the participant meets all study enrollment criteria, she will be enrolled (Appendix C).

**7.3 Study activities and data collection at initial visit**

*7.3.1 Clinical data collection*

At the time of enrollment, information will be collected from each participant on her medical and pregnancy history, and a brief clinical assessment will be performed by a health center staff clinician (see sample data collection form, Appendix D).

*7.3.2 Laboratory sample collection*

Study staff will collect blood from participants for use in study laboratory procedures, and will prepare the samples and conduct the diagnostic tests described; all other care will be provided by health center staff (i.e. clinicians, typically midwives and nurses, employed by the health center). Each participant will provide a 2 mL (two milliliter) venous blood sample for HemoCue hemoglobin (Hb) measurement, preparation of two RDTs, preparation of thick and thin smears for expert light microscopy, and storage in a microtainer and on filter paper for PCR (see further details in section 7.6 below). Hb and RDT results will be used in clinical management as in section 7.3.3 and 7.6.1 below; expert microscopy and PCR results will not be immediately available and will not be used in management.

*7.3.3 Administration of antimalarial medicines*

If both RDT results are negative, the participant will receive a complete dose of SP by directly observed therapy (DOT) on the day of enrollment. If one or both RDTs are positive, she will receive a complete curative dose of ACT or quinine according to the national policy for treatment of parasitemia in pregnancy; the initial dose will be given by DOT, and the remaining doses will be given to the participant with clear instructions for completing the regimen at home. SP or ACT/quinine will be administered by health center clinical staff. If a patient receives curative treatment with ACT or quinine a return visit (or home visit by study staff) to administer a dose of SP will be scheduled for 2 weeks after the end of the curative treatment. The rationale for use of both curative treatment and SP-IPTp for RDT-positive women is as follows: The mode of action of IPTp is not yet completely understood, but is presumed to be two-fold: an IPTp dose *treats* existing asymptomatic infections, and also *prophylaxes* against new infections due to the long half-life of the drug used (e.g. SP). There is some evidence that the primary benefit may result from “intermittent suppressive chemoprophylaxis.”50 Quinine does not have such a prophylactic effect, and while ACTs pair a short-acting artemisinin compound with a longer-acting drug, there is as yet no evidence that ACTs provide a prophylactic effect similar to SP in pregnancy. Therefore, we believe that the safest approach for the current study is to provide both curative treatment, and the currently recommended IPTp drug, i.e. SP. While there are no published data that raise concern for clinically significant drug interactions among these antimalarials, for reasons of tolerability and due to the limited data on pharmacokinetics in pregnant populations we will administer the drugs 2 weeks apart.

*7.3.4 Provision of symptomatic and routine antenatal care*

(See also Uganda site-specific information in section 7.2.) Any symptoms reported by the participant at the time of the initial visit will be investigated and managed according to the local standard of care by the health center staff clinician providing care. Data will be collected on symptoms reported and any treatments given. Each participant will be offered a standard antenatal care package, according to WHO and national guidelines, including iron and folate supplementation, nutritional advice, and a long-lasting insecticide-treated bed net (LLIN); information on provision and use of such care will be recorded at enrollment and in subsequent visits. Each participating health center is affiliated with a network of government- or missionary-sponsored clinics/hospitals providing care free or at reduced cost. The standard of care for any medical problem that exceeds the capacity of the participating center is to refer to a higher level of care. As clearly described during the informed consent discussion, symptom management and referral will be done at the discretion of the health center staff; study staff will not be able to assist financially. Please see paragraph below for Uganda site-specific details on this topic.

***Uganda site-specific information (as requested by WHO; italic font):*** *The usual standard of care for the care and follow-up of pregnant women at TDH follows national guidelines from the Uganda Ministry of Health. Pregnant women are provided, for free according to resource availability, with a standard antenatal care package, including access to the four recommended antenatal visits for basic assessment, symptomatic management (empiric treatment of urinary tract infections and sexually transmitted diseases, analgesics for pain syndromes, and similar), hemoglobin estimation where available, iron and folate supplementation, antihelminth treatment, routine counseling and testing for syphilis and HIV, a long-lasting insecticide-treated bed net (LLIN), and advice and counseling on nutrition and on prevention of sexually transmitted diseases. The standard of care for any medical problem that exceeds the capacity of the participating center is to refer to a higher level of care. Participants in this study will be assured access to components of the basic antenatal package including routine assessment by health center staff, iron and folate supplementation, and a LLIN. As clearly described during the informed consent discussion, symptom management and referral will be done at the discretion of the health center staff. As discussed with the Uganda ethical review committee (Makerere University Faculty of Medicine Research and Ethics Committee), study staff including a clinician may assist with providing standard care to study participants in case of need and in collaboration with health center staff.*

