For purposes of epidemiological investigations, the gold standard for diagnosis of malaria in pregnancy is histopathological examination of the placenta after delivery.15-17 As recently summarized by Rogerson, et al, microscopic observation of histological changes in the placenta, including the presence of hemozoin deposits, may be used to confirm current and previous malaria infections, and a variety of laboratory protocols have been suggested for preparation of such samples.16, 18 A number of studies have documented the low sensitivity of light microscopy of peripheral blood smears for detecting placental infection.19 Importantly, some studies have indicated that submicroscopic malaria infections, identified with PCR or antigen-detection tests, may be associated with negative clinical outcomes including maternal anemia19, 20 and low birth weight.21 However, PCR is not available outside research settings, and antigen-detection tests have not yet been evaluated adequately for use in pregnancy.

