## 4.1 General objective

To determine whether screening pregnant women for malaria with RDTs may detect placental infection and predict risk of poor birth outcomes due to malaria in areas of varied malaria transmission in Africa.

Specific primary objectives:

1. To compare the results of RDTs, microscopy and PCR performed on peripheral blood from women in the second and third trimesters of pregnancy in malaria-endemic areas of Africa.
2. To determine the positive and negative predictive values of results of RDTs, microscopy and PCR performed on peripheral blood from women in the second and third trimesters of pregnancy, as compared with evidence of placental infection by histological examination after delivery.

Specific secondary objectives:

1. To measure and compare the frequency of pregnancy outcomes (infant birth weights, maternal hemoglobin), prevalence of placental malaria, and risk of symptomatic malaria among women in the study cohort. Participants who test positive by RDT at the time of usual IPTp administration will receive artemisinin-combination treatment (ACT) or quinine; participants who test negative by RDT will receive standard-of-care IPTp with SP.
2. To collect samples for future laboratory analyses related to malaria in pregnancy, including the measurement of the prevalence of molecular markers of antimalarial resistance in the study cohorts.
3. **STUDY DESIGN**

(See Figure 1 on next page.) Women will be enrolled at their initial presentation for antenatal care after quickening, i.e. on the first antenatal visit when they are eligible for IPTp according to WHO recommendations.2 On the usual IPTp schedule, typically once in the second and once in the third trimester, blood will be collected from all participants for RDT testing, preparation of thick and thin smears for light microscopy, and PCR. RDTs detecting histidine-rich protein 2 (HRP2) and plasmodium lactate dehydrogenase (pLDH) will be used for testing. All participants with negative RDT results will receive SP, and those with a positive RDT result will receive ACT or quinine (according to national policy for treatment of malaria in pregnancy). All participants will be followed up to delivery. At delivery maternal peripheral and placental blood samples will be collected for RDT testing, light microscopy, and PCR, and placental tissue samples will be processed for histopathological examination. Measurement of maternal hemoglobin and infant birth weight will be obtained.

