**11.2 Analysis plan**

The unit of analysis will be each pregnancy. For each pregnant woman a complete data set consists of the following:

| Variable | Type of data | Variable classification | | | | |
| --- | --- | --- | --- | --- | --- | --- |
| Confounder | Evidence of placental malaria | Outcome measure | | |
| Predictive value of diagnostic | Infant birth weight | Maternal Hb |
| RDT on peripheral blood taken during 2nd trimester | Binary (positive / negative) |  |  | X |  |  |
| Microscopy of peripheral blood taken during 2nd trimester | 1. Binary (positive / negative)  2. Count for positives |  |  | X |  |  |
| PCR on peripheral blood taken during 2nd trimester | Binary (positive / negative) |  | X |  |  |  |
| RDT on peripheral blood taken during 3rd trimester | Binary (positive / negative) |  |  | X |  |  |
| Microscopy of peripheral blood taken during 3rd trimester | 1. Binary (positive / negative)  2. Count for positives |  |  | X |  |  |
| PCR peripheral blood taken during 3rd trimester | Binary (positive / negative) |  | X |  |  |  |
| RDT on peripheral blood taken during or shortly after delivery | Binary (positive / negative) |  |  | X |  |  |
| Microscopy of peripheral blood taken during or shortly after delivery | 1. Binary (positive / negative)  2. Count for positives |  |  | X |  |  |
| PCR result on peripheral blood taken during or shortly after delivery | Binary (positive / negative) |  | X |  |  |  |
| Placental histology for evidence of infection | Binary (positive / negative) |  | X |  |  |  |
| Diagnostic results of any additional visits to clinic (eg symptomatic infection) | Binary (positive / negative) |  | X |  |  |  |
| Maternal Hb at delivery | Continuous |  |  |  |  | X |
| Infant birth weight at delivery | Continuous |  |  |  | X |  |
| Study site | Nominal | X |  |  |  |  |
| Age | Continuous | X |  |  |  |  |
| Gravidity | Ordinal | X |  |  |  |  |
| SP treatment | Binary (yes/no) | X |  |  |  |  |
| Iron & folate supplementation | Binary (yes/no) | X |  |  |  |  |
| Bed net use | Binary (yes/no) | X |  |  |  |  |

The following definitions will be used:

- Evidence of placental malaria: a positive PCR result is obtained for any peripheral blood sample and / or there is evidence of placental infection by histology
- RDT positive: a positive RDT result is obtained from one or more blood samples
- Microscopy positive: parasites are detected by microscopy (thick film) in one or more of the blood samples

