The accuracy of RDTs and peripheral microscopy at detecting placental malaria will be assessed by considering the sensitivity, specificity, positive predictive value and negative predictive value of each diagnostic compared to evidence of placental malaria. This analysis will be conducted for all samples combined and also separately for each study location. Marginal generalized linear models will be developed to assess the impact of confounders on predictive values.

The impact of RDT screening and treatment compared to standard IPT on infant birth weight and maternal Hb will be assessed for non-inferiority by testing the hypotheses:

1. Mean birth weight of infants whose mothers were RDT positive & treated with ACT/quinine ≥ mean birth weight of infants whose mothers were RDT negative (and received SP)
2. Mean Hb of mothers who were RDT positive & treated with ACT/quinine ≥ mean Hb of mothers who were RDT negative (and received SP)

Standard statistical techniques such as t-tests, ANOVA and regression modeling will be used to test these hypotheses and investigate the potential impact of confounders on birth weight and maternal Hb.

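### Only the RDT triggers curative treatment before delivery, so its PPV against histology reflects treatment as well as accuracy and cannot be ranked against PCR's

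*Protocol*

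**What the plan says.** Objective 2 in Protocol 4.1 asks for predictive values of RDT, microscopy and PCR on second- and third-trimester peripheral blood, "as compared with evidence of placental infection by histological examination after delivery".

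Between those tests and the placenta comes treatment. Section 7.3.3 states: "If one or both RDTs are positive, she will receive a complete curative dose of ACT or quinine". A dose of SP follows two weeks after the course ends. When both RDTs are negative the woman receives SP only. Section 7.4.3 repeats the rule for later visits. For the other two tests, 7.3.2 says that "expert microscopy and PCR results will not be immediately available and will not be used in management"; 7.4.2 says the same.

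Section 11.2 then evaluates "the sensitivity, specificity, positive predictive value and negative predictive value of each diagnostic compared to evidence of placental malaria". It counts a woman as a case if "a positive PCR result is obtained for any peripheral blood sample and / or there is evidence of placental infection by histology". Its variable table lists SP treatment as a confounder but has no entry for ACT or quinine. Section 11.1 names PCR as one of the tests whose negative predictive power is a primary outcome, while the 11.2 table places PCR with the evidence of placental malaria.

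**The concern.** One of the three tests under comparison sets the treatment given between the test and the reference reading. Suppose an infection is found by the RDT, treated, and leaves nothing for the pathologist to see. Scored against histology, a correct RDT result becomes a false positive. An infection that the RDT missed but PCR found stays on SP alone and is more likely to remain visible, which counts as a true positive for PCR.

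The study exists to judge whether RDT screening detects placental infection. If objective 2 is reported against histology and read as plain test accuracy, successful treatment counts against the RDT and the comparison with PCR is not like for like. Adjustment for curative treatment would not repair this, because the RDT result itself assigns that treatment.

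**Working it through.** **Inputs.** Sensitivity 0.65 and specificity 0.98 are the design values in 11.3. Prevalence p = 0.25 is an assumption taken from the background figure of about one in four in 3.1.1; no site prevalence is given. PCR sensitivity 0.95 and specificity 0.97, with PCR detecting every infection that the RDT detects, are assumptions. Let c be the share of infected, RDT-positive women whose histology is negative at delivery after curative treatment plus SP, and d the same share among infected, RDT-negative women given SP alone. The protocol gives neither c nor d, nor any figure of its own for this effect.

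**Cells at p = 0.25.**
- Infected and RDT-positive: 0.65 × 0.25 = 0.1625.
- Uninfected and RDT-positive: 0.02 × 0.75 = 0.0150.
- Infected and RDT-negative: 0.35 × 0.25 = 0.0875.
- Uninfected and RDT-negative: 0.98 × 0.75 = 0.7350.

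**Formulas against histology alone.**
- RDT PPV = 0.1625(1−c) / 0.1775. It falls for any c > 0, whatever d is.
- RDT sensitivity = 0.1625(1−c) / [0.1625(1−c) + 0.0875(1−d)]. It falls only if c > d.
- NPV = (0.7350 + 0.0875d) / 0.8225. It does not contain c.

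| c | d | RDT PPV | RDT sensitivity | NPV |
|---|---|---|---|---|
| 0 | 0 | 0.915 | 0.650 | 0.894 |
| 0.1 | 0 | 0.824 | 0.626 | 0.894 |
| 0.2 | 0 | 0.732 | 0.598 | 0.894 |
| 0.3 | 0 | 0.641 | 0.565 | 0.894 |
| 0.2 | 0.2 | 0.732 | 0.650 | 0.915 |
| 0.3 | 0.2 | 0.641 | 0.619 | 0.915 |

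For other prevalences, going from c = 0 to c = 0.3 moves RDT PPV from 0.783 to 0.548 at p = 0.10 and from 0.956 to 0.669 at p = 0.40.

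**PCR against histology.** PCR-positive women are 0.1625 + 0.0750 infected (RDT-positive and RDT-negative respectively) and 0.03 × 0.75 = 0.0225 uninfected, in total 0.2600. PCR PPV = [0.1625(1−c) + 0.0750(1−d)] / 0.2600.
- c = d = 0: 0.913, so PCR minus RDT is −0.002.
- c = 0.3, d = 0: 0.726, so the gap is 0.085.
- c = 0.3, d = 0.2: 0.668, so the gap is 0.027.
- c = d = 0.2: 0.731, so the gap is −0.002 again.

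PCR is thus pulled in the same direction, but by less when c > d. The treatment rule alone can then open a gap between the tests. Microscopy depends on how far its positives overlap with the RDT's, which the protocol does not state.

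**Against the 11.2 composite.** A woman with a positive peripheral PCR stays a case whatever happens later. If PCR detects every RDT-detected infection, c drops out of RDT PPV and sensitivity. But every PCR-positive woman is then a case by definition, so PCR's PPV is 1 by construction and the RDT is in effect being compared with PCR.

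**The case against.** The strongest reply is that 11.2 does not use histology alone. Its composite includes PCR taken before treatment, so a reader who infers that the accuracy figures planned in 11.2 are themselves seriously biased by treatment goes too far. That part of the reply stands. It does not rescue objective 2, which names histology and asks about PCR as a test; the composite cannot answer that.

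Second, section 3.1.2 says histological changes "may be used to confirm current and previous malaria infections", and the heading of 7.6.7 covers prior as well as current infection. A treated infection is lost only if it leaves no trace, so c may be small. This stands, and no passage supports any particular c.

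Third, one might infer that RDT sensitivity must fall. The documents do not support that without a condition. Section 7.3.3 presumes that an IPTp dose also treats existing infection, and with c = d sensitivity does not move. The protocol's own premise of declining SP effectiveness (3.2) makes c > d plausible but does not establish it.

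Fourth, one might infer that the PPV test in 11.3 loses power. That is not supported. Site prevalences are not stated, the enrolment figures cannot be reproduced uniquely without them, and under the composite the loss largely disappears.

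Fifth, not every RDT-positive woman is exposed. The 11.2 definition covers any sample, and its table includes the RDT at delivery, where no RDT-triggered treatment precedes collection of the placenta. Clinicians may also treat symptoms at their discretion (7.3.4, 7.4.4). Both points blur the size, not the direction.

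**Conclusion.** The concern holds for objective 2 when it is reported against histology. RDT PPV is biased down to the extent that treated infections leave no histological evidence. RDT sensitivity is biased down only if curative treatment plus SP removes more evidence than SP alone, and under that same condition PCR is affected less than the RDT. NPV among RDT-negative women, the first primary outcome in 11.1, is not distorted by curative treatment.

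The size cannot be found from the protocol. The fall in histology-only RDT PPV from 0.92 to 0.82–0.64 rests on an assumed 10% to 30% loss of evidence, prevalence of 25% and no clearance in RDT-negative women. It is illustrative and does not describe the composite analysis. What remains is that neither reference, as now written, gives a fair comparison of RDT with PCR: histology because of treatment, the composite because PCR is part of it.

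**What to change.** Amend 11.2, with no change to treatment:

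1. Make the objective 1 comparison visit-specific: RDT and microscopy against PCR on blood from the same visit, drawn before that visit's treatment.
2. Report objective 2 against histology alone, with active-or-past infection as the main reference and active infection shown separately.
3. Present RDT PPV and sensitivity against histology as values obtained under RDT-guided treatment, and do not rank RDT against PCR or microscopy on them.
4. Relate PCR and microscopy to histology within the RDT-negative stratum, defined as women with no positive antenatal RDT, so that nobody in it received RDT-triggered curative treatment. Base the study's conclusion on NPV.

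The cost is wording and a few more tables from samples already planned, provided the histology reading records active and past infection separately. The price is a weaker claim about RDT PPV.

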***(End Uganda site-specific information.)***

*7.3.5 Scheduling of subsequent visit/s*

The participant will be encouraged to return to the study site for her subsequent routine antenatal visit/s, and if feasible, for any intervening care-seeking. Subsequent antenatal visits will be scheduled according to the national standard of care, typically including at least one visit in the second trimester and one visit in the third trimester. Routine visits will be scheduled at least 4 weeks apart; participants will not receive more than one dose of SP within any 4-week period. Each participant will be given a card/booklet with dates of future study visits, and in which to record any care or treatment that is received from non-study site providers between routine visits.

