**RDT positive**

**(either HRP2 or pLDH)**

**RDTs negative**

**(both HRP2 and pLDH)**

- **DOT IPTp with SP**
- Management of any symptoms at clinician’s discretion according to national guidelines and standard of care
- **ACT (according to nat’l policy)**
- Management of any symptoms at clinician’s discretion according to national guidelines and standard of care
- **Follow up 2 weeks later for DOT IPTp with SP**

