**Subsequent routine antenatal visit/s**

(≥ 1 month after previous visit and before onset of labor)

- History & clinical exam
- Venous blood for Hb, RDTs, thick/thin smear, and storage in EDTA, red cell pellet and filter paper for PCR
- Provision of other standardized care (ITN, iron + folate supplementation, etc) according to national guidelines

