**7.4 Study activities at subsequent routine antenatal visits**

*7.4.1 Clinical data collection*

At each subsequent scheduled antenatal visit, information will be collected from the participant on any treatments sought since the previous visit and on current symptoms, and a brief clinical assessment will be performed by a health center staff clinician.

*7.4.2 Laboratory sample collection*

Study staff will collect blood from participants for use in study laboratory procedures, and will prepare the samples and conduct the diagnostic tests described; all other care will be provided by health center staff (i.e. clinicians, typically midwives and nurses, employed by the health center). At each scheduled visit, the participant will provide a 2 mL (two milliliter) venous blood sample for HemoCue Hb measurement, preparation of two RDTs, preparation of thick and thin smears for light microscopy, and storage in a microtainer and on filter paper for PCR (see further details in section 7.6 below). Hb and RDT results will be used in clinical management as in sections 7.4.3 and 7.6.1 below; microscopy and PCR results will not be immediately available and will not be used in management.

*7.4.3 Administration of antimalarial medicines*

If both RDT results are negative, the participant will receive a complete dose of SP by DOT. If one or both RDTs are positive, she will receive a complete curative dose of ACT or quinine (as in section 7.3.3 above); the initial dose will be given by DOT, and the remaining doses will be given to the participant with clear instructions for completing the regimen at home. SP or ACT/quinine will be administered by health center clinical staff. If a patient receives curative treatment with ACT or quinine, a return visit (or home visit by study staff) to administer a dose of SP will be scheduled for 2 weeks after the end of the curative treatment. (See section 7.3.3 for explanation of rationale.)

*7.4.4 Provision of symptomatic and routine antenatal care*

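### A woman who is RDT-positive at one routine visit and RDT-negative at the next, less than about 45 to 49 days later, is due two SP doses inside the protocol's own 4-week limit

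*Protocol*

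**What the plan says.** Four places in the protocol govern when SP is given.

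- **Section 7.3.5 (scheduling).** It sets a minimum visit interval, "Routine visits will be scheduled at least 4 weeks apart", and a limit on dosing, "participants will not receive more than one dose of SP within any 4-week period". It describes the usual schedule as "typically including at least one visit in the second trimester and one visit in the third trimester".
- **Section 7.3.3 (initial visit).** A woman with either RDT positive gets ACT or quinine. The first dose is observed, and "the remaining doses will be given to the participant with clear instructions for completing the regimen at home". A further contact, at the clinic or at home, "to administer a dose of SP will be scheduled for 2 weeks after the end of the curative treatment". Section 7.4.3 repeats this for later visits.
- **Section 7.4.3 (later routine visits).** "If both RDT results are negative, the participant will receive a complete dose of SP by DOT". No exception is written for a woman who had SP recently, and the limit in 7.3.5 is not mentioned. The Study Design section likewise gives SP to all RDT-negative participants.
- **Figure 1.** The RDT-positive branch ends with "Follow up 2 weeks later for DOT IPTp with SP". The next routine visit is placed "≥ 1 month after previous visit and before onset of labor". The figure does not say whether the SP contact counts as a visit for that purpose.

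**The concern.** The 4-week spacing in 7.3.5 runs from one routine visit to the next. For an RDT-negative woman SP is given at the routine visit itself, so visit spacing and dose spacing coincide. For an RDT-positive woman SP is moved to a separate contact more than 2 weeks after the routine visit. The next routine visit may still take place 4 weeks after the first, and if she is then RDT-negative, 7.4.3 calls for SP that day. In that case visit spacing no longer secures the dose limit.

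The main stake is a written dosing limit in pregnant women that another written instruction breaches when followed literally. The protocol does not say whether the second dose or the visit date gives way.

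There is a lesser analytical stake. Only women with a positive RDT can meet this situation, and they form one side of the birth-weight and Hb comparisons in section 11.2. SP enters that analysis as a yes/no variable, although both RDT groups are scheduled to receive SP. The variable would therefore not show differences in the number or timing of doses.

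**Working it through.** **Inputs from the protocol**
- SP limit: at most one dose in any 4 weeks, taken as a gap of at least 28 days (7.3.5).
- Minimum interval between routine visits: 28 days (7.3.5).
- SP after a positive RDT: 14 days after the end of curative treatment (7.3.3, 7.4.3).
- SP after both RDTs negative: the same day (7.4.3).

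**Assumption.** The protocol gives no length for the curative course. Let D be the days from the RDT-positive visit to the end of treatment. I use D = 3 to 7, with D = 0 as a limiting case. The protocol has later doses taken at home, so D = 0 is not a realistic value.

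**Formula.** Day 0 is the RDT-positive routine visit and day V is the next routine visit, RDT-negative.
- First SP: day D + 14.
- Second SP: day V.
- Gap = V − (D + 14).
- The limit is met when V − (D + 14) ≥ 28, that is, when V ≥ 42 + D.

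**Results: gap in days between the two SP doses**

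| Next routine visit (V) | D = 0 | D = 3 | D = 7 |
|---|---|---|---|
| 28 | 14 | 11 | 7 |
| 35 | 21 | 18 | 14 |
| 42 | 28 | 25 | 21 |
| 45 | 31 | 28 | 24 |
| 49 | 35 | 32 | 28 |
| 56 | 42 | 39 | 35 |

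At V = 28 the gap is below 28 days for every D, since even D = 0 gives only 14. The limit is first met at V = 42 (D = 0), 45 (D = 3) or 49 (D = 7). If the one-month spacing in Figure 1 is taken as 30 days between routine visits, the gaps are 16, 13 and 9 days, still too short.

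**Other sequences at 28-day spacing, with the same D each time**
- Negative then negative: SP on days 0 and 28, gap 28.
- Negative then positive: SP on days 0 and 28 + D + 14, gap 42 + D, or 42 to 49 for D = 0 to 7.
- Positive then positive: SP on days D + 14 and 28 + D + 14, gap 28.

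None of these breaks the limit. Only positive then negative does.

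**Starting date of the 2 weeks.** If Figure 1 is counted from the visit, SP falls on day 14. That is 14 − D days after treatment ends: 11 days for D = 3 and 7 for D = 7, against 14 in the text. The gap to a visit on day 28 is then 14 days.

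**The case against.** The strongest reply is that the rules can be met together. Four weeks is a minimum, visits are scheduled in advance, and the usual pattern described in 7.3.5 is compatible with longer intervals. A next visit at 42 + D days or later satisfies every section. This stands. A reader might infer that every RDT-positive woman is dosed inside the limit, or that staff are always forced to break a rule; the documents do not support either inference. But the protocol sets no longer minimum for treated women, and section 7.3.4 mentions four recommended antenatal visits for the Uganda site, so shorter intervals are possible.

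Second, the limit in 7.3.5 is categorical and may be meant to override 7.4.3. That is a reasonable reading, but it is not stated. Nor would it tell staff whether the dose is omitted, the dose is deferred or the visit is moved.

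Third, the one-month spacing in Figure 1 could be counted from the SP contact, which would remove the conflict. The figure leaves this open. However, its box concerns routine visits, 7.3.5 spaces routine visits, and the SP contact may be a home visit that is nowhere called routine.

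Fourth, the 2-week wording in Figure 1 is probably shorthand for the rule in the text. I accept that. It is a loose end to tidy, not a separate contradiction.

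Fifth, the SP given after treatment is not an additional dose. It replaces the dose an RDT-negative woman would have had at the visit itself. That is correct: the problem is its timing relative to the next visit.

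Finally, a reader might infer a bias in the birth-weight or Hb comparison. Nothing in the documents shows one. Site-specific protocols that might settle the handling are mentioned but not available here.

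**Conclusion.** The point holds in a conditional form. When a woman is RDT-positive at one routine visit and RDT-negative at the next, and the interval is at least 28 days but less than 42 days plus the course length, sections 7.3.3 and 7.4.3 taken literally breach the limit in 7.3.5. With an assumed course of 3 to 7 days the upper bound is about 45 to 49 days, and at 28-day spacing the doses are about 7 to 11 days apart. The existence of the conflict does not depend on the assumed course length, because the gap at 28 days cannot exceed 14 days.

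The protocol gives neither the distribution of visit intervals nor the frequency of the positive-then-negative sequence, so the number of women affected cannot be estimated. No sample size, power or significance figure rests on this point. It should still be corrected, because it concerns a stated dosing limit and the correction is cheap. Which rule should prevail is a clinical decision and is not judged here.

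**What to change.** Reconcile sections 7.3.3, 7.3.5, 7.4.3 and Figure 1:

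1. State one rule, chosen by the clinical investigators, for an RDT-negative routine visit that falls within 4 weeks of the post-treatment SP dose, and cross-refer to it from 7.4.3.
2. State whether the SP contact counts as a visit for the one-month spacing in Figure 1.
3. Use one starting date for the 2-week interval in both the figure and the text.

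Optionally, use recorded SP dates to describe the number and timing of doses in the analysis, since the yes/no SP variable in section 11.2 cannot show them. This is a secondary suggestion and not needed to resolve the conflict. The data collection forms are not available here, so whether they already capture these dates cannot be judged.

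The cost is a short protocol clarification, matching text in the visit instructions and, at most, a date field. No extra participants are needed.
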